## Abstract

**Background:**

Diabetic peripheral neuropathic pain (DPNP), affecting ~50% of diabetes patients, imposes major burdens on quality of life and healthcare systems, while current therapies including pharmacotherapy and conventional spinal cord stimulation remain limited by insufficient efficacy and adverse effects. Our study aims to evaluate the clinical efficacy and safety of 10 kHz high-frequency spinal cord stimulation (HF-SCS) compared to traditional low-frequency SCS (T-SCS) in alleviating DPNP.

**Methods:**

This prospective, randomized, controlled, multicenter trial will enroll 100 participants with DPNP. Patients aged 18–80 with chronic (≥6-month) lower limb pain will be randomly assigned to HF-SCS (10 kHz) vs. T-SCS (40–60 Hz). The primary outcome is the treatment efficacy rate, defined as ≥50% reduction in numeric rating scale (NRS) scores at 3 months post-intervention. Secondary outcomes include improvements in quality of life (Short Form 12), sleep quality (Athens Insomnia Scale), psychological status (Beck Depression Inventory), neuropathy severity (Michigan Neuropathy Screening Instrument), and microcirculatory parameters assessed via infrared thermography. Safety evaluations encompass adverse events, laboratory tests, and imaging findings.

**Discussion:**

This study seeks to provide robust evidence on the superiority of HF-SCS in pain relief, functional improvement, and microcirculatory benefits, potentially establishing it as a preferred neuromodulation strategy for DPNP. Findings may advance clinical practice by addressing unmet needs in chronic pain management through targeted, mechanism-driven interventions.

**Clinical trial registration:**

https://www.chictr.org.cn/indexEN.html, identifier: ChiCTR2300078291.

## 1 Introduction

Global diabetes prevalence is projected to increase from 9.3% in 2019 to 10.2% by 2030 and further to 10.9% by 2045 (1). Diabetic peripheral neuropathic pain (DPNP) is a common complication affecting ~50% of individuals with diabetes (2). This condition not only severely impacts patients' quality of life, causing sleep disturbances, depression, and anxiety, but also increases the overall healthcare burden due to high treatment costs (3).

Currently, there is no definitive and effective treatment for DPNP. Conventional therapeutic modalities—including pharmacotherapy, lumbar sympathetic nerve block, and alternative therapies—are typically associated with limited efficacy and frequent side effects (4–6). Furthermore, the complex pathophysiological changes induced by primary diabetes, including oxidative stress, vascular ischemia and hypoxia, and neurotrophic factor deficiency, pose significant challenges for both basic and clinical research on DPNP (7, 8). As a result, targeted treatments for DPNP have yet to achieve significant breakthroughs, making it one of the most pressing clinical challenges.

Spinal cord stimulation (SCS) is an internationally recognized and widely used method for treating chronic refractory pain (9). Traditional SCS (T-SCS) therapy involves implanting stimulating electrodes in the epidural space and delivering low-frequency electrical stimulation at 40–60 Hz to the spinal cord segments corresponding to the pain region. This stimulation produces a tingling sensation, which effectively masks the pain and provides analgesic relief. Numerous clinical studies have demonstrated the efficacy of T-SCS in treating DPNP, confirming its potential as a treatment option (10–12). T-SCS operates based on the Gate Control Theory, which activates amyloid β (Aβ) fibers in the dorsal horn through electrical pulses (13). This activation promotes inhibitory interneuron activity and increases the release of the inhibitory neurotransmitter γ-aminobutyric acid (GABA), which helps block nociceptive signal transmission (14). However, over time, T-SCS often leads to paresthesia and a diminished analgesic effect, limiting its long-term effectiveness (15).

Recent advances in SCS have facilitated the development of high-frequency spinal cord stimulation (HF-SCS). Basic experimental results demonstrate that HF-SCS can reduce mechanical sensitivity with long-lasting analgesic effects after cessation in peripheral nerve injury animal models (16). Additionally, HF-SCS significantly increases vasodilation compared to normal-frequency SCS, potentially through the retrograde stimulation of unmyelinated C fibers and the induced release of calcitonin gene-related peptides (17). HF-SCS mechanisms directly target DPNP pathogenesis, establishing a pathophysiological rationale for clinical use. Based on this, our study aims to evaluate HF-SCS vs. T-SCS for DPNP, providing evidence to support HF-SCS clinical application.

## 2 Methods and analysis

### 2.1 Study design

This prospective randomized controlled multicenter study will enroll 100 participants recruited competitively from multiple centers, with equal randomization (*n* = 50/group) to either HF-SCS (H-group) or SCS (C-group) therapy. The trial comprises three phases: baseline evaluation, 10–14-day intervention period, and 3-month post-operation follow-up. The flow chart is shown in Figure 1 by Figdraw. All participant characteristics and clinical outcomes will be documented using case report forms (CRFs). Data collection procedures are outlined in Table 1.

**Figure 1 F1:**
[figure not shown]
Flowchart of the study.

**Table 1 T1:** Schedule of data collection.

**Procedure**	**Screening period**	**Intervention**	**Follow-up period**	
	**Visit1**		**Visit2**	**Vist3**
	**Day−7 to 0**	**Day 0**	**Day 14 ±5**	**Day 90 ±7**
Informed consent	X			
Demographic information	X			
Physical examination	X		X	X
Vital signs	X		X	X
Vertebral X-ray	X		X	
ECG	X		X	
NRS	X		X	X
MNSI	X		X	X
SF-12	X		X	X
AIS	X		X	X
BDI	X		X	X
Glycosylated hemoglobin	X			
Insulin and C-peptide	X			
Routine blood test	X		X	
Liver and kidney function	X		X	
Lower limb infrared thermography	X		X	X
Randomization	X			
Surgical operation		X		
Adverse event	X		X	X
Combined medication	X		X	X
Treatment records	X		X	X

ECG, Electrocardiogram; NRS, Numerical Rating Scale; MNSI, Michigan Neuropathy Screening Instrument; SF-12, 12-Item Short Form Health Survey; AIS, Athens Insomnia Scale; Beck, Beck Depression Inventory.

### 2.2 Sample size

According to the results of RCT studies comparing HF-SCS with traditional SCS for the treatment of PDPN, the efficacy rate of HF-SCS for PDPN is ~86%. Based on the statistical sample size calculation method for superiority trials, with a one-sided significance level (α) of 0.025, a test power (1-β) of 0.8, and an equal sample size ratio between the treatment group and the control group, the required sample size for each group was calculated using PASS 17.0 to be 45 cases. Considering a 10% loss to follow-up and refusal rate, at least 50 cases are needed in the treatment group and 50 cases in the control group, resulting in a total sample size of 100 cases.

### 2.3 Inclusion criteria

Participants who meet all the following requirements will be enrolled:

(1) Diagnosed with diabetes mellitus, aged between 18 and 80 years.(2) Symmetrical distal pain in the lower limbs, with or without dysesthesia.(3) PDPN duration >6 months.(4) Pain characterized as prickling, electric shock-like, and/or burning sensations.(5) Abnormal results in Quantitative Sensory Testing (QST).(6) Presence of hyperalgesia and/or allodynia.(7) No abnormality in lower limb reflexes and muscle strength.(8) No spinal canal abnormalities (e.g., stenosis) on MRI or CT imaging.

### 2.4 Exclusion criteria

Participants who meet one of the following requirements will be excluded:

(1) Concomitant severe cardiovascular or cerebrovascular diseases.(2) History of lumbar spine surgery or traumatic spinal canal stenosis within the past 6 months, or prior lumbar surgery/traumatic spinal canal stenosis that may interfere with spinal cord stimulation (SCS) procedures or pain assessment in this study.(3) Presence of radicular symptoms.(4) Other spinal abnormalities (e.g., benign/malignant tumors, congenital spinal anomalies, spondylolisthesis).(5) Coagulation disorders, malignancy, active infection, or psychiatric disorders.(6) Pregnancy.

### 2.5 Criteria for discontinuation

During this trial, subjects experiencing the following conditions will be considered as dropout cases, and the reason and date of dropout will be recorded in a case report form.

(1) Violation of inclusion/exclusion criteria at enrollment, with the investigator determining compromised participant safety.(2) Participant intolerance to the treatment regimen.(3) Adverse event (AE) occurrence leading to investigator-determined unsuitability for continued study treatment.(4) Major protocol deviations (e.g., non-compliance with study procedures) affecting safety or efficacy assessments.(5) Pregnancy.(6) Withdrawal of informed consent: if a participant withdraws consent; the investigator must document the scope of withdrawal (e.g., discontinuation of treatment only vs. withdrawal from all study procedures/follow-ups) in medical records.(7) Loss to follow-up: defined as failure to attend visits and inability to contact the participant despite ≥2 documented contact attempts at ≥1-week intervals.(8) Early termination of study treatment: discontinuation of treatment while continuing study procedures/follow-ups (if applicable).(9) Early study withdrawal: complete discontinuation of all study-related activities, including treatment and follow-ups (e.g., due to consent withdrawal or loss to follow-up).(10) Follow-up for AE/SAE-related withdrawals: participants withdrawing due to treatment-emergent adverse events (TEAEs) or serious adverse events (SAEs) must be followed until resolution (return to baseline/stable status) or until the AE is deemed clinically insignificant by the investigator.

### 2.6 Randomization and blinding

Competitive enrollment will be conducted across centers. An independent statistician at each center will perform centralized randomization using a validated centralized randomization system. Participants will be randomly assigned to either the HF-SCS group or the T-SCS group at a 1:1 allocation ratio, based on a computer-generated random number.

Due to the distinct sensory profiles between HF-SCS and T-SCS, effective blinding of participants and outcome assessors was not feasible; therefore, only data statisticians were maintained under blinded conditions throughout the study.

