### 3.2 Postoperative management

Participants will return to the ward for stimulation parameter adjustment (HF-SCS group: 10 kHz; T-SCS group: 40–60 Hz). Postoperative instructions will include avoidance of movements that may lead to electrode displacement (e.g., heavy lifting, overhead arm motions, hyperextension). The electrode will remain in place for 10–14 days under the therapeutic stimulation mode before removal, marking the end of the treatment phase.

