## 4 Outcome

### 4.1 Primary outcome

The treatment efficacy rate, defined as a reduction of ≥50% in the numeric rating scale (NRS) score at 3 months post-treatment compared to the pre-treatment score, will be evaluated as primary outcomes.

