In this study, we adopted rigorous methodological strategies to enhance the reliability and validity of our findings. First, randomization and blinding procedures were employed to minimize potential bias and confounding factors. Second, comprehensive outcome measures, including primary efficacy parameters (such as significant reduction in Numeric Rating Scale pain scores) and multidimensional secondary endpoints—such as quality of life (SF-12), psychological status (Beck Depression Inventory), sleep quality (Athens Insomnia Scale), and neurological function improvement (Michigan Neuropathy Screening Instrument)—were selected to capture holistic therapeutic effects on patients with DPNP. Furthermore, the protocol innovatively integrates infrared thermography as an objective assessment modality to holistically evaluate physiological alterations following clinical symptom resolution. Infrared thermography can assess abnormal thermal distribution and temperature differences in various medical conditions caused by alterations in peripheral cutaneous circulation (27). DPNP is closely associated with microcirculatory alterations. HF-SCS's proposed ability to improve microcirculation and nerve health potentially differentiates it from traditional, symptom-oriented interventions. If our findings confirm significant improvements in clinical symptoms, quality of life, and microcirculatory parameters with HF-SCS, it would strongly support its adoption as a superior treatment modality for DPNP.

In conclusion, this randomized controlled trial is anticipated to provide robust clinical evidence regarding the comparative efficacy, safety, and potential pathophysiological benefits of 10 kHz HF-SCS relative to traditional low-frequency SCS for patients suffering from refractory DPNP. Positive outcomes from this trial would signify an important advancement in chronic pain management, potentially shifting clinical practice toward a more effective and patient-preferred neuromodulation strategy.

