## 8 Limitations

This study also has limitations. First, although the study was rigorously designed, potential biases from patient expectations and placebo effects remain, particularly due to differing paresthesia perceptions between HF-SCS and T-SCS. Therefore, infrared thermography will serve as an objective biomarker to complement clinical assessments. Second, due to resource constraints, our follow-up period was set at 3 months. While this duration is sufficient to assess short-term therapeutic effects, it may not fully evaluate long-term treatment outcomes. Third, the stringent inclusion criteria may restrict the generalizability of our findings to broader DPNP populations. Therefore, real-world studies with extended follow-up and expanded patient populations will be conducted in the future.

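### Section 2.6 leaves every outcome assessor unblinded for a reason that applies only to the patient, so thermograms and the Day 90 MNSI examination are assessed open without need

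*Protocol article*

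**What the plan says.** All references are to the protocol article.

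- **Section 2.6** gives one reason, the difference in sensation between the two modes, and draws one conclusion for two groups of people: "effective blinding of participants and outcome assessors was not feasible; therefore, only data statisticians were maintained under blinded conditions throughout the study".
- **Section 3.2** fixes the end of stimulation: "The electrode will remain in place for 10–14 days under the therapeutic stimulation mode before removal, marking the end of the treatment phase".
- **Section 4.1** sets the primary outcome as a responder rate, "defined as a reduction of ≥50% in the numeric rating scale (NRS) score at 3 months post-treatment compared to the pre-treatment score". Table 1 places Visit 3 at Day 90 ±7.
- **Section 4.2** lists the secondary outcomes: SF-12, AIS, BDI, MNSI and leg thermography. Thermography is done before surgery, at 2 weeks and at 3 months.
- **Section 8** concedes that patient expectation and placebo effects may bias the results, and answers that "infrared thermography will serve as an objective biomarker to complement clinical assessments".
- **Section 7** lists among the trial's strengths that "randomization and blinding procedures were employed to minimize potential bias and confounding factors".

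**The concern.** The reason and the decision do not match. A difference in sensation explains why a patient cannot be kept unaware of the mode. It does not explain why someone who reads a stored image, or examines a patient's feet more than two months after the electrode is out, must know the arm. Section 2.6 does not merely pass over assessor blinding. It rules it out, and names the statisticians as the only blinded group.

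The consequence is sharpest for thermography. Section 8 relies on it as the measure that patient expectation cannot reach. If the person who reads or processes the images knows the arm and the visit, reader expectation can take the place of patient expectation, and the safeguard is weaker than claimed. An examiner who knows the arm can likewise colour the Day 90 neuropathy examination. Meanwhile Section 7 tells the reader that blinding has reduced bias, although neither patients nor assessors are blinded.

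**Working it through.** The plan gives no figure for this point, so there is none to reproduce. The check is one of dates and of who is exposed to what.

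**Inputs**
- Surgery: Day 0 (Table 1).
- Electrode in place: 10–14 days (Section 3.2), so removal is on about Day 10–14.
- Visit 2: Day 14 ±5 (Table 1), that is Day 9–19.
- Visit 3: Day 90 ±7 (Table 1), that is Day 83–97.

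**Time from removal to Visit 3**
- Shortest: earliest visit minus latest removal = 83 − 14 = 69 days.
- Longest: latest visit minus earliest removal = 97 − 10 = 87 days.

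If the 3 months of Section 4.1 were counted from the end of treatment instead of from surgery, the interval would be longer, which does not weaken the point.

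**Time from removal to Visit 2**
- Earliest visit minus latest removal = 9 − 14 = −5 days.
- Latest visit minus earliest removal = 19 − 10 = +9 days.

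At Visit 2 the electrode may still be in place, so the argument from removal holds for Visit 3 and not reliably for Visit 2.

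**Does the sensory reason reach each assessment?**

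| Assessment | Who produces the value | Does the sensory difference prevent blinding? |
|---|---|---|
| NRS, SF-12, AIS, BDI | Patient report (assumed usual use) | Yes for the patient, who remembers the sensation; an interviewer's influence is separate and avoidable |
| MNSI, examined part (assumed examiner-rated) | Examiner | Not at Visit 3; at Visit 2 the electrode may still be in place |
| Thermograms, all three time points | Reader of a stored image | No; the reader need not meet the patient, and this does not depend on removal |

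**Volume of coding work:** 100 patients × 3 time points = at most 300 image sets.

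**Section 7 against Section 2.6:** the first credits blinding with limiting bias; the second limits it to "only data statisticians were maintained under blinded conditions throughout the study". The Section 7 sentence is not literally false, since the statisticians are blinded, but a reader would take it to mean more than Section 2.6 allows.

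**The case against.** The strongest counter-argument is that little of this touches the primary endpoint. Pain on the NRS is the patient's own report, patients do not forget 10–14 days with or without tingling, and they may tell an assessor which they had. Expectation on the patient's side is largely unavoidable here and Section 8 discloses it. This stands. It confines the point mainly to secondary outcomes and, for the NRS, to possible interviewer influence. It also rules out an inflated false-positive rate as the measure of size: any assumed shift in reporting between arms would include the unavoidable patient part.

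A patient may also reveal the arm to an MNSI examiner. That makes examiner blinding imperfect but not pointless, and it does not affect coded images.

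A reader might go further on the timing of randomisation, which the document does not support:

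- *That the baseline NRS is contaminated.* Table 1 marks randomisation and the baseline scales in the same Visit 1 column (Day −7 to 0). Nothing places randomisation first, and the document does not say when the arm is disclosed to the patient or surgeon.
- *That randomisation should wait until the lead is in and coverage is confirmed.* Section 3.1 describes one operation, and the first stated difference between arms comes afterwards: "Participants will return to the ward for stimulation parameter adjustment (HF-SCS group: 10 kHz; T-SCS group: 40–60 Hz". But Section 3.1 also connects an external generator, and the article does not say that both arms use the same one. Waiting for coverage would also make it an entry condition, change the population, and leave some patients implanted but never randomised. That is a trade-off, not a correction.
- *That early allocation costs a known share of patients.* The document gives no rate of failure to implant or to obtain coverage.

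**Conclusion.** The point holds in a limited form. The only reason Section 2.6 gives for open assessors does not extend to the reading of thermograms at any visit, or to the MNSI examination at Visit 3, which takes place 69–87 days after stimulation ends. Section 7 overstates the blinding that Section 2.6 provides.

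The size of the bias cannot be computed from the document. The improvement mainly protects secondary outcomes, above all thermography, on which Section 8 relies. Patient expectation in the self-reported primary NRS would remain.

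The conclusion rests on three assumptions: that removal follows surgery by the stated 10–14 days, that the MNSI includes an examiner-rated part, and that reading or processing the thermograms leaves some room for judgement. The article does not describe the last two. This is a cheap improvement worth making and does not threaten the validity of the primary comparison.

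**What to change.** 1. **Section 2.6, thermography:** state that thermograms from all visits are read from coded files with arm and visit hidden.
2. **Section 2.6, Visit 3:** state that the NRS and questionnaires are self-completed before contact with the treating team, and that the MNSI is examined, where existing staffing allows, by site staff who took no part in programming.
3. **Table 1:** add a note that the baseline scales are completed before the randomisation call. This settles an order that the table leaves open, and leaves the time of randomisation as it is.
4. **Section 7:** say that only the statisticians and, after change 1, the thermogram readers are blinded.

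The cost is the coding of at most 300 image sets and some scheduling at Visit 3. No visit, procedure, additional staff or change to treatment is needed. Where a centre has no uninvolved examiner, the MNSI stays open there and the report should say so.

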## 3 Procedure

### 3.1 Surgical procedure

Participants will undergo the following standardized surgical protocol in the operating room: multiparameter physiological monitoring will be initiated, and intravenous access will be established. The participant will be positioned prone, followed by standard antiseptic preparation and draping. Under C-arm fluoroscopic guidance, the target intervertebral space corresponding to the spinal nerve innervating the painful area will be identified. After achieving satisfactory local anesthesia, an epidural puncture will be performed via a lateral approach. The needle will be advanced through the interlaminar space into the epidural space. A spinal cord stimulation (SCS) electrode will be implanted, followed by intraoperative external SCS testing to confirm paresthesia coverage overlapping the painful area. The electrode lead will be secured at the puncture site with sutures and covered with sterile dressing. The electrode extension cable will be connected to an external pulse generator.

### 3.2 Postoperative management

Participants will return to the ward for stimulation parameter adjustment (HF-SCS group: 10 kHz; T-SCS group: 40–60 Hz). Postoperative instructions will include avoidance of movements that may lead to electrode displacement (e.g., heavy lifting, overhead arm motions, hyperextension). The electrode will remain in place for 10–14 days under the therapeutic stimulation mode before removal, marking the end of the treatment phase.

